### Assignment of interventions: allocation

#### Sequence generation {16a}

After inclusion criteria of patients with cSDH has been satisfied and written informed consent form has been obtained, randomization is allowed. Patients will randomly be assigned to trial arms using a web platform and an extended stratified block algorithm. The algorithm guarantees even distribution of key baseline characteristics across the intervention and the control group.

#### Concealment mechanism {16b}

Participants are randomized using the Research Electronic Data Capture (REDCap), a web-based, GCP compliant electronic data capture (EDC) system for collecting patient data in clinical trial, observational studies, and registries. The software REDCap is a secure, browser-based web application available to approximately 2.3 million users in 151 countries [25]. It maintains allocation concealment as it does not release the randomization code until screening has been completed and the patient was cleared to be recruited onto the trial.

#### Implementation {16c}

Extended stratified block algorithms generate an unpredictable allocation sequence. Random assignment by REDCap [25] cannot be influenced by clinical investigators.

### Assignment of interventions: blinding

#### Who will be blinded {17a}

Due to open-label trial design, the treatment allocation is known to both the treating physician and the patient. In each center is nominated a blinded expert physician that will procure the information concerning clinical outcome at 3, 6 and 12 months. Radiological assessment is also performed by blinded and trained neuroradiologist evaluating non contrast CT scan (NCCT) after 3, 6 and 12 months from randomization. To report to the data safety monitoring board (DSMB), outcome data will be combined with data on treatment allocation by an independent trial statistician. Members of the steering committee are kept blinded of results of interim analyses of efficacy and safety.

#### Procedure for unblinding if needed {17b}

N/A. We do not anticipate any requirement for unblinding but if required, the Trial Manager, Data Coordinator, Implementation Support Facilitators and Care Home Managers will have access to group allocations and any unblinding will be reported.

### Data collection and management

#### Plans for assessment and collection of outcomes {18a}

Data will be entered by physician and supporting trial personnel on electronic case report forms (eCRFs). Clinical examination comprises the mRS and Markwalder scale for neurologic disability. Standard laboratory parameters will be taken from peripheral blood at baseline and during planned follow-up. The size and extent of cSDH will be measured on the coronal scans of NCCT, at the point of maximum thickness of the blood collection.

#### Plans to promote participant retention and complete follow‑up {18b}

Investigators, doctors, and nurses will take very care of all trial participants until the scheduled last follow-up visits. Patients will also be explained there is scientific evidence that patients included in a clinical trial environment may show superior outcomes compared to those managed under routine practice conditions.

#### Data management {19}

All patient data is registered in the electronic data capture software REDCap. This worldwide online system allows built-in logical checks and validations to promote data quality. All clinical data are entered via an encrypted connection, are anonymized, and fulfill the demands for data protection. All data entries and changes are logged in REDCap [25] and meet the Good Clinical Practice (GCP) requirements for the use of the electronic case report form (eCRF) in medical trials. Trial coordinators, data managers and the investigators will be introduced to the platform and trained in data entry during the initial kick-of meeting prior to recruitment of the first patient. Trial staff will be provided with a personal ID.

#### Confidentiality {27}

All study-related information will be stored securely in every participating center. All participant information will be kept in a locked space to which only the principal investigator has access and may be used to unblind personal data if necessary. Data processing and statistical work will be performed by exporting the data from REDCap to a secure server. Participant confidentiality will always be maintained.

#### Plans for collection, laboratory evaluation and storage of biological specimens for genetic or molecular analysis in this trial/future use {33}

N/A as no biological specimen is collected as part of this trial.

### Statistical methods

#### Statistical methods for primary and secondary outcomes {20a}

Categorical data were presented as frequencies and percentages and compared using the Chi-square test or Fisher’s exact test where appropriate. Continuous variables were expressed as median, deviation standard [DS] and interquartile range [IQR] and compared using a two-tailed Mann–Whitney test for non-parametric distributions. The primary outcome analysis is to evaluate treatment failure rate of mild symptoms cSDH (Markwalder scale 0−1) within 6 months follow-up post randomization and to determine whether MMA embolization is superior to conservative management. Analysis will be performed on an ‘intention-to-treat’ principle. The chi-square test or Fisher’s exact test will be used as primary analysis to test the difference in primary outcome between the experimental and control groups. Moreover, odds ratio (OR) with 95% confidence intervals will be calculated by a logistic regression model. Binary second efficacy outcomes will be analyzed using the same method as primary endpoint analysis. Procedure-related complications and (serious) adverse events (AEs/SAEs) will be expressed as absolute and relative frequencies.

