#### Sample size {14}

Our estimates are based on treatment failure rates of previous published studies. Ban et al. [18] compared a prospective series of 72 patients with cSDH submitted to MMA embolization with a group control of 469 subjects undergoing standard treatment. In particular, in the amount of patients into embolization group, 27 (37.5%) were asymptomatic and underwent MMA embolization alone. No treatment failure was found during follow-up after embolization. Of 469 patients in the control group, 67 patients underwent close follow-up. Spontaneous resolution occurred in 11 (16.4%), but treatment failure with surgical rescue was needed in 56 (83.6%) for symptom development resulting from progression of hematoma. Moreover, Catapano et al. [21] reported a treatment failure rate of 17% and of 3%, respectively with conservative approach and MMA embolization. Other studies reported progression rate of conventional treatment ranged from 11 to 27.5% [22–24]. So we assume the event rate of the intervention group is 1%. The trial is powered to assess superiority. When assuming the event rate of 1% in intervention group and 10% event rate in the control group, with a power of 85% and two-sided alpha of 0.05, allowing for 10% drop-outs, the estimated sample size is 300 patients in total.

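### Randomisation is stratified, but the named primary test is an unstratified chi-square or Fisher test with no stated criterion for choosing: some power may be lost, though type I error is not inflated

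*Protocol article*

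**What the plan says.** Sequence generation {16a} of the protocol article describes the allocation: "Patients will randomly be assigned to trial arms using a web platform and an extended stratified block algorithm". It gives the purpose as balance: "The algorithm guarantees even distribution of key baseline characteristics across the intervention and the control group". The article does not list the factors.

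Statistical methods {20a} fixes the primary analysis as one of two tests, chi-square or Fisher's; the sentence ends "exact test will be used as primary analysis to test the difference in primary outcome between the experimental and control groups". That sentence has no stratum or covariate term and no rule for choosing. The opening sentence of the section, on categorical data in general, does add Fisher's "exact test where appropriate", but without a criterion. Separately, an "odds ratio (OR) with 95% confidence intervals will be calculated by a logistic regression model"; its covariates are not stated. Binary secondary efficacy outcomes follow the method of the primary endpoint.

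Sample size {14} sets the event rates: "When assuming the event rate of 1% in intervention group and 10% event rate in the control group". It asks for 85% power at a two-sided 5% level, adds a 10% allowance for drop-out and arrives at a total of 300.

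**The concern.** Two things are at issue, and both concern what the article states rather than what it leaves out.

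- **Strata.** Stratified randomisation forces the arms to be balanced on the chosen factors. If those factors predict failure, the true variance of the treatment difference is smaller than a pooled two-by-two test assumes. The pooled test then uses too large a standard error, rejects less often than 5% under the null, and gives up power that the design has already paid for.
- **Choice of test.** Chi-square and Fisher's test can give different answers when failures are few, which is what this trial plans for. Without a written criterion, a borderline result could be reported as significant or not, depending on a choice that the article does not settle.

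The stake is efficiency and a clearly defined primary p-value. It is not the validity of a positive result.

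**Working it through.** **Inputs.** From Sample size {14}: 1% and 10% failure, power 85%, two-sided alpha 0.05, 10% drop-out, total 300. From Trial Design {8}: 1:1 allocation. Stratum-specific failure rates are not in the document, so those used below are assumptions.

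**1. Reproduce the planned size.** With mean rate 0.055:

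n₀ = [1.960·√(2·0.055·0.945) + 1.036·√(0.01·0.99 + 0.10·0.90)]² / 0.09² = 0.9206 / 0.0081 = 113.7 per arm.

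With continuity correction: n = (n₀/4)·[1 + √(1 + 4/(n₀·0.09))]² = 28.4 × (1 + √1.391)² = 135.0 per arm.

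Then 2 × 135 = 270 and 270 / 0.90 = 300. The planned total reproduces, with 135 evaluable patients per arm.

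**2. Compare the two permitted tests.** All two-by-two tables with 135 per arm were enumerated, each weighted by its binomial probability.

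| True rates | Chi-square rejects | Fisher rejects | Opposite sides of 0.05 |
|---|---|---|---|
| 1% vs 10% (design) | 94.8% | 90.4% | 4.4% |
| 3% vs 10% | 66.7% | 56.4% | 10.3% |
| 5.5% in both | 4.8% | 2.4% | 2.5% |
| 10% in both | 5.1% | 3.1% | 2.0% |

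(3% is an embolization failure rate that Sample size {14} itself cites.) Examples, as failures with embolization versus control:

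- 0 vs 5: chi-square p = 0.024, Fisher p = 0.060.
- 1 vs 7: 0.031 and 0.066.
- 2 vs 9: 0.031 and 0.060.

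In all 258 discordant tables chi-square is the significant test. Fisher alone never is.

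**3. Compare pooled chi-square with CMH.** Simulation with about 135 per arm, equal-sized strata and 1:1 balance within each.

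| Assumed control rates by stratum | Effect | Power, pooled | Power, CMH |
|---|---|---|---|
| 2%, 18% | risk ratio 0.1 (1% vs 10% overall) | 95.1% | 95.5% |
| 20%, 60% | risk ratio 0.6 | 82.0% | 85.2% |
| 10%, 70% | risk ratio 0.6 | 84.1% | 91.0% |

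The gains are 0.4, 3.2 and 6.9 points. Under the null, the pooled test rejects in 4.2% to 4.7% of trials with prognostic strata averaging 10%, in 3.4% with strata of 20%/60%, and in 1.5% with 10%/70%. CMH stays at about 5% throughout. The direction is always conservative.

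**4. Check how sparse the data would be.** Expected failures at the design rates are 135 × 0.01 + 135 × 0.10 = 1.35 + 13.5 = 14.85. The chance of no failure at all in the embolization arm is 0.99¹³⁵ = 26%. In that case ordinary maximum-likelihood logistic regression has no finite treatment estimate.

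**The case against.** The strongest reply has four parts.

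- **The article is condensed.** Stratification factors, covariates of the logistic model and selection thresholds may stand in a full protocol or SAP that is not shown. This holds for those details, and their absence is not counted here. It does not cover the primary test itself, which {20a} names outright in a form that ignores the strata. An SAP that stratified it would contradict this text.
- **The choice is not wholly open.** The general remark in {20a} is commonly read as Fisher when an expected count is below 5. With equal arms the expected failures per arm are half the pooled count, so that rule means fewer than 10 failures in total and does not depend on the treatment difference. At the design rates Fisher would then apply in 6.6% of trials, discordant tables governed by Fisher would occur in 0.8%, and power would be 94.0%. This largely stands: the 4.4% is the room left by an unwritten rule, not the expected rate of conflict under the usual one. The article still does not state the rule.
- **No false-positive gain.** A reader might infer that picking the better p-value inflates type I error. It does not. Because chi-square is the significant test in every discordant table, picking the smaller p-value is the same as always using chi-square, whose size is 4.8% at a common rate of 5.5% and 5.1% at 10%.
- **Baseline data are used.** A reader might also infer that baseline hematoma information is thrown away. It is not: baseline thickness is the reference value in the primary outcome (Outcomes {12}), and side enters the additional analyses {20b}. These variables are only absent from the primary test.

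**Conclusion.** The point holds in a limited form and is worth correcting. The primary test does not match the stratified design, and its selection criterion is unwritten. The consequence is conservatism and lost efficiency, so a significant result from the planned analysis would remain valid.

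It would be wrong to read a large power loss into the plan as designed: at 1% versus 10% the gain from stratifying is under 1 point. The 3 to 7 points arise only if control failure is far more common and the effect smaller than planned. The article's own figures make more frequent control failure plausible. Outcomes {12} counts any thickness reduction of 50% or less as failure, the Background {6a} reports spontaneous resolution in only 3% to 18%, and Sample size {14} cites 83.6% failure in one closely followed control group. It also cites 11% to 27.5% progression elsewhere, so the rate is uncertain. The stratum rates in the simulation are assumptions; since the factors are not named, the actual loss cannot be computed. If they are not prognostic, there is essentially none.

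**What to change.** In {20a}:

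- Name one primary test: CMH stratified by the randomisation factors.
- Fix in advance when its exact version is used, for example when the pooled failure count is below a stated number. Without that number, the fallback would recreate the same undefined choice.
- Take the odds ratio and its confidence interval from the same stratified analysis, so that estimate and p-value agree.
- Keep the crude chi-square as a sensitivity analysis.
- Put baseline maximum thickness and unilateral or bilateral side only in a supporting regression, fitted by a sparse-event method such as Firth or exact logistic regression. With about 15 expected failures, ordinary logistic regression with added covariates is too fragile to be primary.

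The cost is a change of wording and slightly more programming. No new data are needed and the total stays at 300. If events are as rare as planned, the gain in power will be small; what remains is a primary analysis that matches the design and leaves no choice open.

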### Trial Design {8}

Embotrial-1 is an Italian multicenter prospective randomized clinical trial with open-label treatment and blinded outcome assessment (PROBE) to assess the superiority of MMA embolization compared to conservative treatment. The intervention group is MMA embolization and comparator control group is the conservative management and best medical treatment. Patients are randomized 1:1. Patient flowchart is depicted in Fig. 1.

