#### Methods for additional analyses (e.g., subgroup analyses) {20b}

Primary and secondary outcomes will be stratified in a categorical manner for age (≤60 and >60 years), arterial hypertension, anticoagulant and antiplatelet home therapy and ipsilateral or bilateral side of hematoma.

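### Under the plan's own 1% failure rate, the embolization arm has a 22% to 26% chance of no failures, and an ordinary logistic fit then gives no finite log odds ratio and no usable Wald interval

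*Protocol article*

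**What the plan says.** The section on statistical methods for primary and secondary outcomes {20a} tests the primary outcome by chi-square or Fisher's exact test. It then adds an effect estimate: "odds ratio (OR) with 95% confidence intervals will be calculated by a logistic regression model". Binary secondary efficacy outcomes are to be handled in the same way. Categorical data are also presented as counts and percentages.

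The sample size section {14} fixes the rates by "assuming the event rate of 1% in intervention group and 10% event rate in the control group". It sets 85% power at the two-sided 5% level, expects one patient in ten to be lost, and arrives at 300 patients overall. The trial design section {8} adds that "Patients are randomized 1:1".

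The section on additional analyses {20b} says "Primary and secondary outcomes will be stratified in a categorical manner for age", and lists hypertension, antithrombotic home therapy and side of hematoma as further factors. It gives no subgroup sizes.

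The article names no method for an arm with zero events, and no confidence interval for an absolute difference.

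**The concern.** The estimator and the design assumption fit each other badly. A 1% failure rate in an arm of 135 to 150 patients means one or two expected events, so an empty cell is a real possibility. Logistic regression fitted in the usual way, by maximum likelihood with Wald limits, breaks down when one arm has no events.

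The breakdown would fall on the trial's most favourable results. Embolization would have no failures and the primary test would almost certainly be significant, yet the one effect estimate named in the plan would come out as a non-converged coefficient with an absurd standard error. A replacement estimator would then be chosen after the data were seen. The abstract and discussion say the trial is to weigh benefit against risk, and that needs an effect size with a stated precision.

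**Working it through.** **Inputs.** From {14}: 1% and 10% failure, 85% power, two-sided alpha 0.05, 10% drop-out, 300 patients. From {8}: 1:1 allocation. This gives 150 randomized per arm and 150 × 0.90 = 135 evaluable.

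**Step 1: reproduce the plan's sample size.** With mean rate 0.055 and difference 0.09, the uncorrected number per arm is

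[1.960 × √(2 × 0.055 × 0.945) + 1.036 × √(0.10 × 0.90 + 0.01 × 0.99)]² / 0.09² = (0.632 + 0.328)² / 0.0081 ≈ 113.7.

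With the continuity correction: (113.7 / 4) × [1 + √(1 + 4 / (113.7 × 0.09))]² ≈ 135 per arm, 270 in total. Then 270 / 0.90 = 300, which matches. The inputs are therefore read as the plan intended.

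**Step 2: expected events.** Embolization: 135 × 0.01 = 1.35, or 150 × 0.01 = 1.5. Control: 135 × 0.10 = 13.5, or 150 × 0.10 = 15.

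**Step 3: chance of no failures in the embolization arm**, (1 − p)^n:

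| True rate p | n = 135 | n = 150 |
|---|---|---|
| 0.5% | 50.8% | 47.1% |
| 1% (plan) | 25.7% | 22.1% |
| 2% | 6.5% | 4.8% |
| 3% | 1.6% | 1.0% |
| 5% | 0.1% | 0.05% |

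In the control arm the chance is below one in a million (0.90^135), so it adds nothing.

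**Step 4: what the ordinary fit returns.** Take 0/135 against 14/135, with 14 being 13.5 rounded up. The sample odds ratio is (0 × 121) / (135 × 14) = 0, so its logarithm is minus infinity. A standard maximum-likelihood fit failed to converge and stopped at a coefficient of −29.6 with a standard error of about 686,000. Adding covariates would not help, because the treatment term still has no finite estimate.

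**Step 5: what happens to the primary test.** Fisher's exact test on the same table gives p = 0.00009. Given no embolization failures in 135 and a 10% control rate, the two-sided Fisher test is significant with probability 99.4%. So 0.257 × 0.994 = 25.6% of trials run exactly as assumed would be positive without a finite log odds ratio.

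**Step 6: what other methods give for that table.**

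- Upper 95% limit for the odds ratio: about 0.28 (exact conditional) or 0.13 (profile likelihood).
- Firth estimate: for an unadjusted two-by-two table this equals adding 0.5 to each cell, so (0.5 / 135.5) / (14.5 / 121.5) = 0.031.
- Newcombe risk difference: the Wilson intervals are 0 to 2.77% for 0/135 and 6.28% to 16.66% for 14/135. The difference is −10.37 points. The lower limit is −10.37 − (16.66 − 10.37) = −16.7. The upper limit is −10.37 + √(2.77² + (10.37 − 6.28)²) = −5.4.

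All of these are usable where the ordinary fit is not.

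**The case against.** **A sparse-data fallback is commonly left to the SAP, which is not shown.** The article says only that a logistic regression model will be used; it specifies neither maximum likelihood nor Wald limits. Firth and exact regression are logistic models too. This stands in part: the fix clarifies {20a} rather than contradicting it. But {20a} does fix the effect measure and model, and read in the ordinary way they suit the plan's own event rate poorly.

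**The trial would still have a result.** This stands. A reader might infer that a positive trial could end with nothing to report. The documents do not support that. The chi-square or Fisher test is primary and unaffected, failures are reported by arm as counts and percentages, and exact or profile upper limits for the odds ratio exist. What is lacking is a named method for the odds ratio in this case, and an interval for the absolute difference.

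**The 1% assumption is fragile.** This also stands. The sample size section cites a 3% failure rate with embolization in one series, although none of 27 patients embolized alone failed in another. The primary outcome counts a thickness reduction of 50% or less as failure, and also counts rescue surgery before embolization. The discussion accepts that the latter may inflate failures in this arm. If the true rate is 2% or 3%, the problem shrinks as Step 3 shows.

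**An odds ratio is a legitimate measure.** Agreed. Making the risk difference the main effect measure would be a choice of scale, and nothing in the plan makes the odds ratio an error.

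**Conclusion.** The point holds for the effect estimate only. Under the plan's own 1% rate, the chance of no failures in the embolization arm is 22% if all 150 randomized patients are analysed, which is the stated intention-to-treat set, and 26% if 135 are evaluable. In that event an ordinary logistic fit gives no finite log odds ratio and no usable Wald interval. Power and the primary significance test are not in question.

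The figure rests on the 1% rate, on independent patients, and on the usual maximum-likelihood fit. With 135 per arm it drops to 6.5% at 2% and 1.6% at 3%.

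Two stronger readings should be avoided. Zero failures are possible but not likely: at the planned rate at least one failure occurs in 74% to 78% of trials. And although splitting the arm by the factors in {20b} makes empty cells more common, the documents give no subgroup sizes and prescribe no odds ratio within subgroups, so no subgroup probability can be stated from them.

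The change is worth making before results are seen, because it is nearly free and works at any event rate.

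**What to change.** In {20a}:

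- Keep the chi-square or Fisher test as the primary analysis.
- State that the odds ratio will come from Firth-penalised logistic regression with profile penalised-likelihood 95% limits, or from exact logistic regression.
- Add the risk difference with a Newcombe or Miettinen-Nurminen 95% interval alongside the odds ratio.
- Apply the same methods to binary secondary outcomes and to the subgroups in {20b} where cells are empty or small.

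If the unseen SAP already names such a method, a reference to it in {20a} is enough.

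Cost: one or two sentences and slightly more analysis work in standard software. The Firth estimate is shrunk a little towards no effect. No additional patients or data are needed, and the sample size is unchanged.
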